#### Safety endpoints

For safety assessments, we are diligently monitoring adverse events at each visit, following the guidelines outlined in the Patient Reported Outcomes version of the Common Terminology Criteria for Adverse Events from the National Cancer Institute^24,25^. Safety Endpoints in this clinical trial encompass the following: (i) Time to the first occurrence of the adverse events (AE): (a) Liver injury, evaluated both overall and individually by causative factors (defined as ALT or AST levels ≥ 5x Upper Limit of Normal [ULN], or the combination of ALT or AST ≥ 3x ULN with bilirubin ≥ 2x ULN measured in the same blood sample); (b) Ketoacidosis, assessed both overall† and categorized by baseline diabetes status; (c) Lower limb amputations, considered overall† and differentiated by level (toe, forefoot, foot, below knee, or above knee); (ii) Time to the first occurrence of another AE relevant to the study’s objective: (a) Bone fracture, examined both overall and categorized by site (long bones versus non-long bones) and etiology (distinguishing those resulting from high and low impact trauma, and other causes); (b) Symptomatic dehydration, defined by whether participants experience symptoms attributable to dehydration, such as feeling faint or fainting; (iii) Time to the first occurrence of hospitalization, categorized by specific causes according to the MedDRA Primary System Organ Class (SOC); (iv) Time to the first occurrence of Serious Adverse Events (SAEs), both overall† and separately, by Primary SOC category; (v) Discontinuation of study treatment, assessed overall and categorized by various causes, including SAEs, non-serious adverse events, and other reasons, using Primary SOC categories for SAEs and non-serious adverse events.

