### Clinical care protocol

The study protocol, outlined in Fig. 1, begins with patient referrals from local dialysis clinics to our research center, where undergo their initial medical assessment to determine eligibility. During this visit, a certified physician presents the informed consent form and conducts a thorough interview to gather medical history register, followed by a comprehensive physical examination. Then, participants are randomly assigned in a 1:1 ratio either dapagliflozin (10mg/day) plus standard treatment or standard treatment alone (control group) using an automated system.

Furthermore, peripheral blood samples are collected for biochemical analysis, and a 12-lead electrocardiogram is obtained. Blood pressure readings are taken in triplicate after 3 minutes of rest in a seated position and repeated after 1 minute of standing to assess orthostatic changes, using the Omron Hbp-1120 device (Omron Healthcare, Japan). Additionally, assessments through dual X-ray absorptiometry (DXA), bioimpedance, echocardiography, gait speed measurement, and six-minute walk test are performed during this visit.

Once the baseline evaluation is completed, patients in the dapagliflozin group receive the necessary pills for a 24-week treatment period, and all participants are thereupon contacted monthly to report outcomes and monitor medical adherence until study’s conclusion, at which baseline evaluations are repeated.

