### Follow-up

Following randomization, participants receive monthly phone calls over a six-month period. During each contact, they are queried about various aspects, including changes in their dry weight, alterations in bowel and urinary habits, their overall well-being during daily activities, blood pressure measurements, occurrences of fractures, any medical procedures undergone, initiation of new treatments, surgeries, hospitalizations, infections, and clinical incidents. Additionally, participants in the dapagliflozin group are required to report the number of study drug pills taken in the past 30 days to track medication adherence, which is registered as a percentage.

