### Efficacy endpoints

The primary endpoint of our study is the between-groups differences in posttreatment changes in plasma levels of NT-proBNP. Secondary endpoints encompass the differences between groups in the changes of LV mass, EF, E/e’ ratio, KCCQ points, 6-min walk test distance, gait speed, lean to fat mass ratio, and handgrip strength.

In addition, an exploratory analysis will be conducted, in which participants with residual diuresis will be inquired about changes in their urinary output. Furthermore, the incidence of a composite outcome comprising cardiovascular death, hospitalization for heart failure, and stroke will be compared between the dapagliflozin and control groups. Changes in serum levels of bone metabolism markers, such as FGF-23 and a-Klotho, as well as on bone mineral density, will be compared between groups as an exploratory analysis.

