Mineral bone disorders (MBD) contribute to cardiovascular disease progression in dialysis recipients.^46^ Phosphate overload elicits intricated downstream effects on calcium metabolisms prompting arterial media and cardiac valves calcification, hyperparathyroidism-induced ventricular hypertrophy and arrythmia, and osteopenia.^46^ Impaired expression of klotho protein plays an imperative role in the progression of MDB, and this event was attenuated by treatment with SGLT2i *in vivo*.^47,48^ SGLT2i- related changes in klotho and other bone metabolism markers will be analyzed, as well as changes in bone mineral density, compared to standard treatment as an exploratory analysis of this trial.^49^

It is important to acknowledge the limitations inherent of this study. Ethical considerations precluded the prior administration of dapagliflozin to dialysis recipients. Consequently, we have decided for the open-label design, recognizing its shortcomings compared to double-blinded trials. To counteract potential biases stemming from this choice, our evaluators, responsible for conducting echocardiography, cardiopulmonary tests, and biochemical analysis are blinded to patients’ allocation. Also, upon completion of the study, an independent statistician will analyze the dataset devoid of any study group information. Of note, previous breakthrough studies in ESKD, such as the ASCEND-D and INNO2VATE trials, have employed similar study designs.^50,51^

In conclusion, the DARE-ESKD-2 will yield unique insights into the cardiovascular impact of dapagliflozin in dialysis receivers, encompassing both functional and structural myocardial parameters. These findings hold the potential to pave the way for improved clinical outcomes among patients with ESKD.

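### Symptomatic dehydration is counted only when symptoms are attributed to dehydration, in an open-label trial whose listed blinding does not reach event ascertainment

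*Protocol article*

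**What the plan says.** Under Safety endpoints, the article lists time to first occurrence of adverse events relevant to the study's objective. One of them is "Symptomatic dehydration, defined by whether participants experience symptoms attributable to dehydration, such as feeling faint or fainting". It gives no objective criterion for this endpoint and does not say who makes the attribution. In the same list, liver injury is defined by transaminase and bilirubin thresholds.

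Adverse events are monitored at visits under a patient-reported version of a standard toxicity classification. Between visits, "all participants are thereupon contacted monthly to report outcomes and monitor medical adherence" (Clinical care protocol). The call topics under Follow-up are put to everyone and include "initiation of new treatments, surgeries, hospitalizations, infections, and clinical incidents". One further item goes to one arm only: "participants in the dapagliflozin group are required to report the number of study drug pills taken in the past 30 days".

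The comparator is standard treatment alone. The Discussion says: "Consequently, we have decided for the open-label design, recognizing its shortcomings compared to double-blinded trials". Its countermeasures are that "our evaluators, responsible for conducting echocardiography, cardiopulmonary tests, and biochemical analysis are blinded to patients’ allocation", and that an independent statistician analyses a dataset without group labels.

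Blood pressure is also taken seated and then "repeated after 1 minute of standing to assess orthostatic changes". This is part of the baseline evaluation, which is repeated at the end of the study. The orthostatic change is not among the safety endpoints.

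**The concern.** An endpoint that needs a causal judgement on a subjective symptom is safest when whoever makes the judgement does not know the treatment. Here the participant, who reports the symptom, knows it. The Introduction attributes the benefit of this drug class mainly to natriuresis and glycosuria with better volume control. Anyone who knows that rationale may be readier to read faintness as dehydration in a participant taking dapagliflozin. The same episode in a control may be put down to something else, such as fluid removal at dialysis. That alternative cause is general clinical background and is not stated in the article.

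If attribution differs by arm, the definition itself produces a difference between arms, or hides a real one, in an endpoint that the article treats as relevant to its objective. The blinded statistician cannot undo this, because the label is fixed before the data reach the analysis.

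**Working it through.** The article gives no expected rate for this endpoint, so there is no figure to reproduce. The check has two parts.

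**1. Does any stated safeguard cover the judgement?**

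- Participant: knows the arm (open label, no placebo).
- Caller: blinding is not stated. A caller who asks the pill-count item knows that participant's arm.
- Visit monitoring of adverse events: patient-reported, so it still rests on a participant who knows the arm.
- Blinded evaluators: echocardiography, cardiopulmonary tests and biochemistry only.
- Blinded statistician: acts after events have been labelled.

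None of the stated safeguards reaches the attribution step.

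**2. What could differential attribution do?**

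From the article: 80 participants allocated 1:1, so 40 per arm; p < 0.05; chi-square test for categorical data. Assumed, because the article gives no figures: the true symptom rate t, equal in both arms, and the probability a that a symptom is attributed to dehydration. As a simplification, the endpoint is treated as a proportion rather than as time to first event.

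Recorded proportion = t × a in each arm. With equal t, the recorded risk ratio is a(drug) / a(control), whatever the sample size. The chance of p < 0.05 comes from exact binomial enumeration of the uncorrected chi-square test, with z = |x1 − x2|/n ÷ √(p(1 − p) × 2/n), where n = 40 and p is the pooled proportion.

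| True rate, both arms | Attribution, drug v control | Recorded | Risk ratio | Chance of p < 0.05 |
|---|---|---|---|---|
| 10% | 50% v 50% | 5% v 5% | 1.0 | 4.3% |
| 10% | 60% v 40% | 6% v 4% | 1.5 | 6.1% |
| 10% | 80% v 40% | 8% v 4% | 2.0 | 11.6% |
| 20% | 50% v 50% | 10% v 10% | 1.0 | 5.9% |
| 20% | 60% v 40% | 12% v 8% | 1.5 | 10.2% |
| 20% | 80% v 40% | 16% v 8% | 2.0 | 20.8% |
| 40% | 50% v 50% | 20% v 20% | 1.0 | 5.1% |
| 40% | 60% v 40% | 24% v 16% | 1.5 | 14.6% |
| 40% | 80% v 40% | 32% v 16% | 2.0 | 39.2% |

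The effect can also run the other way. With true rates of 30% on drug and 20% in controls, attribution of 40% and 60% gives 0.30 × 0.40 = 12% and 0.20 × 0.60 = 12%, so a true risk ratio of 1.5 disappears.

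A single trial may show nothing formally. If 12 of 40 in each arm have symptoms and attribution is 60% against 30%, the expected counts are 7.2 and 3.6. Taken as 7 against 4 of 40, the pooled proportion is 11/80 = 0.1375 and z = 0.075 / √(0.1375 × 0.8625 × 2/40) = 0.97, so p is about 0.33. The distortion would then sit in the estimate and not in the p-value.

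**The case against.** The best defence is that the article acknowledges the open-label weakness, puts the same event questions to both arms and does not rely on calls alone. It also counts first hospitalizations and serious adverse events overall, so a faint serious enough to qualify is captured whatever its presumed cause. The rates above are assumed, moderate differential attribution raises the false-positive chance only modestly, and nothing shows that differential attribution occurs. All of this stands. It limits the weight of the point but does not remove it, because non-serious episodes still pass through the attribution rule.

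A reader might infer more than the article supports:

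- **That only faintness counts.** Faintness and fainting are given as examples. The restriction is the attribution, not the list of symptoms.
- **That the calls are unblinded and the drug arm is questioned more about events.** Caller blinding is not stated, and the extra item is a single pill count. Nothing shows that it prompts event reports.
- **That the whole safety comparison is biased.** Liver injury has laboratory thresholds. Amputation and the overall counts of hospitalizations and serious events do not use this attribution.
- **That the composite is biased too.** The article says that "the incidence of a composite outcome comprising cardiovascular death, hospitalization for heart failure, and stroke will be compared", as an exploratory analysis. The composite does not use the dehydration wording. How deaths and admissions are classified is detail that an article may leave to the full protocol, so the lack of a described adjudication process is no finding.

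**Conclusion.** The point holds for one endpoint. As defined, symptomatic dehydration depends on a causal judgement about a subjective symptom. At least the participant knows the arm, and the listed blinding does not extend to event ascertainment. The endpoint is open to differential attribution; the document does not show that such bias is present.

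Its size and direction cannot be known from the article. Under the assumed true rates of 10% to 40%, attribution of 60% against 40% gives a spurious risk ratio of 1.5 and a 6.1% to 14.6% chance of p < 0.05. Attribution of 80% against 40% gives a ratio of 2.0 and 11.6% to 39.2%. These figures show what is possible and are not a forecast. The primary endpoint and the composite are not part of this conclusion.

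**What to change.** 1. In both arms, record every faintness or fainting episode with one identical question, whatever the presumed cause, and flag whether it occurred during or after a dialysis session.
2. Report this all-cause count alongside the existing attributed definition rather than in its place. The trial is ongoing, so state the date of the change and separate participants or follow-up time before and after it.
3. Ask the dapagliflozin-only pill-count item after all event answers have been recorded.
4. Report the between-arm difference in orthostatic blood pressure change at the final visit as a supportive objective measure. It is scheduled only at baseline and study end, so it cannot replace a time-to-event endpoint.

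The cost is a revised call script, one added field and one added table row; no new procedure is needed. There are two downsides. Faintness related to dialysis will dilute a true drug effect in the all-cause count, which is why the attributed definition should be kept beside it. Participant self-report also stays unblinded, so cause-neutral recording removes the attribution step but not all reporting bias.

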### Power and sample size

Based on previous trials involving dapagliflozin, the sample size was meticulously calculated, considering an expected between-groups difference of 9% in the primary endpoint of the relative change of NT-proBNP. With a significance level (alpha). Set at 0.05 and a statistical power (beta) of 80%, the calculation indicated a requirement of 26 patients in each arm, totaling 52 participants. However, in anticipation of potential dropouts and with consideration for secondary outcomes, researchers opted for a more robust sample size of 80 patients. The calculations were performed using G*Power 3.1 Mac version (Heinrich-Heine-Universität, Germany).

### Data management

Data management in our study relies on the utilization of the Research Electronic Data Capture tool (REDCap, Nashville, TN), which is a web-based and secure platform. REDCap serves the critical function of facilitating the auditing of data collection processes and the seamless export of data. This ensures the creation of de-identified datasets, which is a paramount for safeguarding the confidentiality of our study participants.^26^ The principal investigator assumes the pivotal role of compiling a comprehensive summary of examination results, which is the distributed to all participants involved in the study. Additionally, the principal investigator is responsible for delineating the specific roles of sub-investigators within the research team.

### Statistical analysis

Unless specified otherwise, all analyses will entail an intention-to-treat comparison involving all randomized participants. The groups will be compared in terms of their differences from baseline using analysis of covariance (ANCOVA) or rank analysis of covariance (RANKOVA) according to the data distribution and considering baseline values and study arm as covariates. Continuous variables will be expressed as mean ± standard deviation (SD) for normally distributed, or as median (interquartile range) for non-normally distributed data. Categorical data will be presented as counts and percentages. We will employ Student’s t and Mann-Whitney tests to compare means and medians between groups, respectively, while categorical data will be assessed using the chi-square test. Continuous variables may undergo ranking or log-transformation as needed to achieve normality. Adjustments by covariates will be made when appropriate. A statistical significance will be defined as a p-value less than 0.05. The statistical analysis will be carried out using SPSS version 28.00 for Mac, and it will be performed by an accredited statistician.

## DISCUSSION

The DARE-ESKD-2 trial promises to yield groundbreaking insights into the cardiovascular impact of dapagliflozin in patients with ESKD. Building upon the findings of our prior trial, which firstly investigated the pharmacokinetics and safety profile of this drug in individuals undergoing hemodialysis and peritoneal dialysis, our current study aims to uncover the potential cardiovascular benefits of SGLT2i in ESKD.^10^

One significant factor in cardiovascular health among dialysis receivers is the fluid overload on the heart, resulting in abnormal myocardial stretching prompting higher levels of circulating natriuretic peptides (NP).^27^ In a large meta-analysis of 19,000 patients receiving renal replacement therapy (RRT), those in the highest quintile of N-terminal pro–B-type NP (NT-ProBNP) levels experienced a six-fold increase in cardiovascular mortality and a three-fold higher all-cause mortality compared to those in the lowest quintile.^28^ Furthermore, the annual risk of sudden cardiac death increases 5% per each 1ng/mL rise in NT-ProBNP levels. Notably, NT-ProBNP levels also inversely related to indexed left ventricle (LV) mass and diastolic dysfunction grade in ESKD.^28,29^ Additionally, the extent to which NT-ProBNP levels are reduced following an intervention is markedly related to the prevention of cardiovascular death and heart failure-related hospitalization, which are pivotal factors contributing to RRT-related mortality.^30–32^ Hence, the primary outcome of this trial will be difference in NT-proBNP change between the groups.

Structural heart disease affects nine out of ten dialysis receivers, exerting with a substantial impact on long-term mortality rates.^2^ Roughly, half of these patients suffer from LV diastolic impairment, one-third experience right ventricle dysfunction, and about 20% progress to heart failure with reduced ejection fraction (HFrEF).^33,34^ In non-RRT patients, treatment with SGLT2i led to a significant reduction in LV end-diastolic volume (LVEDV) and indexed LV mass by 10mL and 5g/m^2^, respectively, while increasing left ventricular ejection fraction (LVEF) by 2%.^35^ These changes mirror the effects of SGLT2i on myocardial energy supply, ketonemia, suppression of cardiomyocyte death pathways, and improvements in myocardial flow reserve and vasomotor responses.^35–39^ However, the influence of SGLT2i on myocardial function and heart structure, as assessed by echocardiography, has yet to be evaluated in dialysis patients, making it an integral part of the exploratory analysis in this trial.

Dialysis significantly impacts the quality of life (QoL) and functional capacity of patients. Those undergoing RRT are more prone to developing anxiety and depression, and their exercise tolerance is diminished compared to age-matched controls.^40,41^ This study will evaluate QoL through the KCCQ score, which previous studies have shown to be positively influenced by dapagliflozin in patients with HFrEF.^42^ Furthermore, we will assess cardiopulmonary performance using measures such as the 6-minute walk test distance, handgrip strength, and gait speed, while accounting for changes in body composition measured by DXA. Each of these measures hoolds significant prognostic value and has been shown to be influenced by SGLT2i treatment, making posttreatment changes a crucial aspect of this trial’s exploratory analysis.^43–45^

Mineral bone disorders (MBD) contribute to cardiovascular disease progression in dialysis recipients.^46^ Phosphate overload elicits intricated downstream effects on calcium metabolisms prompting arterial media and cardiac valves calcification, hyperparathyroidism-induced ventricular hypertrophy and arrythmia, and osteopenia.^46^ Impaired expression of klotho protein plays an imperative role in the progression of MDB, and this event was attenuated by treatment with SGLT2i *in vivo*.^47,48^ SGLT2i- related changes in klotho and other bone metabolism markers will be analyzed, as well as changes in bone mineral density, compared to standard treatment as an exploratory analysis of this trial.^49^

It is important to acknowledge the limitations inherent of this study. Ethical considerations precluded the prior administration of dapagliflozin to dialysis recipients. Consequently, we have decided for the open-label design, recognizing its shortcomings compared to double-blinded trials. To counteract potential biases stemming from this choice, our evaluators, responsible for conducting echocardiography, cardiopulmonary tests, and biochemical analysis are blinded to patients’ allocation. Also, upon completion of the study, an independent statistician will analyze the dataset devoid of any study group information. Of note, previous breakthrough studies in ESKD, such as the ASCEND-D and INNO2VATE trials, have employed similar study designs.^50,51^

In conclusion, the DARE-ESKD-2 will yield unique insights into the cardiovascular impact of dapagliflozin in dialysis receivers, encompassing both functional and structural myocardial parameters. These findings hold the potential to pave the way for improved clinical outcomes among patients with ESKD.

## Figures and Tables

**Figure 1 F1:**
[figure not shown]
Study protocol.
